## Abstract

**Background:**

School cafeterias can promote poor eating habits, as these retail outlets have a variety of foods considered to be nonnutritive and unhealthy. However, despite the need for effective preventive strategies, there is still disagreement on the best approach due to the lack of evidence on interventions to prevent and treat obesity in the school settings.

**Objective:**

We aim to verify the efficacy of an educational intervention program to improve the hygienic conditions and the composition of the menu offered in school cafeterias in the state of Rio Grande do Sul, Brazil.

**Methods:**

We will conduct a randomized, parallel, two-arm, community-based controlled study. Elementary and high schools, both public and private, in the State of Rio Grande do Sul, Brazil, that have a cafeteria will be eligible. Schools will be recruited and randomly assigned to the intervention (n=27) or control (n=27) group. The intervention group will receive an educational intervention program based on the guidelines issued by the Ministry of Health of Brazil, consisting of a 160-hour distance-learning qualification course, for 10 weeks, and using the Moodle platform and WhatsApp app. The intervention targets the owners and people in charge of the cafeterias, food handlers, principals, vice principals, teachers, pedagogical coordinators, dietitians, representatives of students' parents, and students over 16 years old. Meanwhile, the control group will receive only a printed copy of the book containing the guidelines used. The efficacy of the intervention will be determined by the hygienic conditions of the cafeteria and the composition of the menu offered, also considering the levels of processing of food sold. All outcomes will be analyzed as intention-to-treat and per-protocol. We will use covariance analysis or a generalized linear model for continuous data and ordinal logistic regression for ordinal categorical data. The level of statistical significance considered will be P<.05 for a 95% CI.

**Results:**

This project was funded in early 2018. We administered the intervention program in 2019. All data have already been collected, and we are analyzing the data. The results are expected in 2021.

**Conclusions:**

To our knowledge, this may be the first randomized controlled study in school cafeterias held in Brazil. The results will provide evidence for the formulation of public food and nutritional security policies and for the development of effective strategies to provide safe and healthy school meals.

**Trial Registration:**

Brazilian Clinical Trials Registry RBR-9rrqhk; https://ensaiosclinicos.gov.br/rg/RBR-9rrqhk

**International Registered Report Identifier (IRRID):**

DERR1-10.2196/22680

## Introduction

Childhood obesity has been recognized as one of the greatest public health challenges of the 21st century, according to the World Health Organization [1]. By 2016, 18% of children and adolescents aged 5 to 19 years were overweight or obese worldwide [1]. Data from the Global Burden of Disease Study indicate that more than 70 countries have doubled their prevalence of obesity between 1980 and 2015, with an increase to 112 million obese children worldwide [2].

In Brazil, access to food in the school environment can occur through school meals provided by the Brazilian National School Feeding Program (PNAE - Programa Nacional de Alimentação Escolar) as well as through school cafeterias (ie, a facility within the educational establishment that aims at providing food to the school community upon payment). Data from the 2015 Brazilian National School Health Survey report that the percentages of foods considered unhealthy consumed by Brazilian students are high. The consumption of sweets, ultra-processed snacks, soft drinks, and fried snacks was 41.6%, 31.3%. 26.7%, and 13.7%, respectively [3]. The same survey revealed that these items are mostly unhealthy, nutrient-poor, and unsuitable for health promotion at school.

Studies indicate that school cafeterias end up promoting unhealthy eating habits [4,5]. A high prevalence of foods with low nutritional quality marketed in these places was identified in several observational studies in Brazil [4,6-8], as well as in other countries [9-12]. Given this scenario, evidence indicates that school interventions can have an impact on the prevention or treatment of obesity, with changes in the nutritional status and eating behavior of children and adolescents [13-17]. There is some evidence of effective interventions for better school meals; however, several systematic reviews reveal heterogeneous, low-quality studies with methodological deficiencies and very small effect sizes [12,18-23]. Moreover, few studies have addressed intervention strategies to improve the food environment of school cafeterias [10,24-27]. In addition, the maintenance of long-term effects is not yet known, and large-scale interventions can pose a considerable challenge, limiting their impact on nutrition and public health [18,26,28-30].

According to local government regulations, school food service employees must undergo food safety training [31,32]. The involvement of the entire school community in the development of these interventions is promising for the promotion of an adequate and healthy diet [33,34]. However, studies report that insufficient training appears to be a barrier to adequate food security practice [35]. Review studies suggest that food safety education training is effective for improving the knowledge of food handlers, but more evidence is needed to improve behavior change [36,37].

To the best of our knowledge, there has been no randomized controlled trial conducted in school cafeterias in Brazil. Addressing this gap, we have been developing an educational intervention program with a multicomponent strategy to improve the hygienic conditions and composition of the menu offered in school cafeterias in the state of Rio Grande do Sul, Brazil.

## Methods

This protocol is reported in accordance with the statement of the Consolidated Standards of Reporting Trials (CONSORT) [38] and Standard Protocol Items: Recommendations for Interventional Trials (SPIRIT) [39]. We will conduct a randomized, parallel, two-arm, community-based controlled study in school cafeterias in the state of Rio Grande do Sul, Brazil. The Research Ethics Committee of the Federal University of Rio Grande do Sul (report 89504618.9.0000.5347) approved this project, which was registered in the Brazilian Platform of Clinical Trials under the code RBR-9rrqhk on April 30, 2018 (Universal Trial Number U1111-1213-1614).

### Recruitment and Eligibility Criteria

A total of 330 schools will be assessed for eligibility to participate in the study. The definition of these schools will be obtained through data from the Education Department of the State of Rio Grande do Sul [40]. Confirmation or updates of the existing data will be verified by phone calls to all schools. We will invite to participate elementary and high schools of the public and private sectors located in the Cidadania Noroeste Colonial region, State of Rio Grande do Sul, Brazil, which total 36 municipalities according to the last official census [41].

Schools will be eligible to participate if they have a school cafeteria and they show interest in participating in the research upon signature of a consent form. Schools with exclusive care for children with special needs will be excluded, as they require a different standard of care. Schools will not be excluded based on other characteristics such as size, socioeconomic indicators, and others. Eligibility criteria will be applied prior to randomization.

Eligible schools will be personally invited to participate in the study by the research team. This strategy will be used to ensure the desired sample size. The school principal will sign a consent form for participation. In the case of outsourced cafeterias, we will request the consent of its owner. Each school will nominate its representatives to participate in the study. The principal will be responsible for obtaining the consent of the nominated members.

### Sampling

The sample size calculation was based on primary outcomes. For a significance level of 5% and statistical power of 90% to detect an effect magnitude (*d*) of 0.90, 54 schools will be needed, considering 27 for the intervention group and 27 for the control group. We considered a 10% sample loss to estimate an increase in the sample size. The estimated number of participants required to achieve the study objectives was also based on the study by Nathan et al [24], which aimed at examining whether a theoretically conceived multicomponent intervention was effective in enhancing the implementation of a healthy cafeteria policy in Australian primary schools. The sample size calculation was performed using the Power and Sample Size software (HyLown Consulting LLC, Atlanta, GA).

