### Randomization and Allocation

Randomization will use a minimization process [42] to balance the number of schools between the 2 groups. This approach ensures an excellent balance between groups for several prognostic factors, even in small samples. According to Egbewale [43], the minimization process makes the evaluated groups similar in important characteristics, mainly in trials that involve a small sample and have several prognostic factors to be balanced [38,44]. This procedure decreases the chances of significant discrepancies in baseline prognostic factors that may occur at random [45]. Minimization also controls the imbalances in baseline variables more efficiently than simple randomization, since, in small samples, simple randomization can produce a biased and misleading effect [43,46].

To maintain the balance between groups and prevent disproportionate distribution from occurring, 4 predictors of interest for the allocation will be considered: city, cafeteria administration (school-owned versus outsourced), school scope (public versus private), and the number of students (<500 students versus ≥500 students). An independent researcher will perform the randomization by minimization using a computer-generated technique in SPSS 26 (IBM Corp, Armonk, NY), avoiding possible influence on the allocation. The randomization unit will be schools with cafeterias.

As it will be an educational intervention, the researchers in charge of administering the interventions and assessing the outcomes will not be able to be blinded. Therefore, to avoid interference between the control and intervention groups, blindness will be arranged for the statistician in charge of data randomization and analysis. Participant flow during each stage of the study can be seen in the estimated study flowchart in Figure 1.

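### 27 schools per arm is the 90%-power number with no losses, so the stated 10% loss allowance is not in it; with that loss, power is about 86%

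*Protocol article*

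**What the plan says.** The Sampling section of the protocol article sets the significance level at 5% and the power at 90%, "to detect an effect magnitude (*d*) of 0.90", and concludes that "54 schools will be needed, considering 27 for the intervention group and 27 for the control group". The next sentence adds: "We considered a 10% sample loss to estimate an increase in the sample size". No second, larger figure follows.

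The Methods paragraph of the abstract uses the same number for allocation: "Schools will be recruited and randomly assigned to the intervention (n=27) or control (n=27) group". Under Randomization and Allocation, "The randomization unit will be schools with cafeterias", so the school is the unit throughout and no clustering factor enters the calculation.

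The Sampling section does not say whether the test is one- or two-sided. The abstract pairs the significance level with a confidence interval, "The level of statistical significance considered will be P<.05 for a 95% CI", which points to a two-sided 5% test.

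**The concern.** A reader of the Sampling section will take 54 as a number that already protects 90% power against losing one school in ten. The inputs are all printed, so this can be checked directly, and 27 per arm turns out to be the requirement with every school followed up. The abstract randomises that same 27 per arm, which leaves no visible room for the allowance.

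What is at stake is how the result is read. If schools are lost at the rate the plan itself assumes, the chance of missing a true effect of d = 0.90 is about 14%, not 10%, and a null result would be credited with more power than the design had. Loss is a realistic prospect: the course asks for 16 hours a week for 10 weeks without payment, and the Intervention Group section describes measures to limit drop-out.

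**Working it through.** **Inputs.** From the Sampling section: significance level 0.05, power 0.90, d = 0.90, equal arms, 10% loss. Two-sided testing is inferred from the 95% confidence interval in the abstract; the one-sided case is tried below.

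**Step 1: reproduce the plan's figure.**

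- Normal approximation: n per arm = 2 × (z₀.₉₇₅ + z₀.₉₀)² / d² = 2 × (1.960 + 1.2816)² / 0.90² = 25.94, so 26 per arm (52 schools).
- Two-sample t-test (noncentral t): n = 26.94, so 27 per arm (54 schools). Power is 88.9% with 26 per arm and 90.06% with 27.

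The t calculation reproduces the plan's 27 per arm exactly, with no loss in it.

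**Step 2: add the stated 10% loss.** Divide by 1 − 0.10.

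- t-test: 27 / 0.90 = 30 per arm, 60 schools.
- Normal approximation: 26 / 0.90 = 28.9, so 29 per arm, 58 schools.

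Multiplying by 1.10 instead (29.7 and 28.6) gives the same 30 and 29 after rounding up. Neither method gives 54.

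**Step 3: what 54 randomised schools deliver after 10% loss.** 27 × 0.90 = 24.3, about 24 per arm.

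| Schools per arm analysed | Power at d = 0.90, t-test | Power, normal approximation |
|---|---|---|
| 27 | 90.1% | 91.1% |
| 24.3 | 86.7% | 88.0% |
| 24 | 86.3% | 87.7% |

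With 24 per arm, the chance of missing d = 0.90 is 100 − 86.3 = 13.7%, and the effect detectable with 90% power is d = 0.956.

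**Step 4: could another reading give 27 with the loss included?**

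- *One-sided 5% test.* The t-test needs 21.86, so 22 per arm; 22 / 0.90 = 24.4, so 25 per arm. That is not 27. Under such a test 24 per arm would have 92.3% power, but then 27 would not be the number the formula gives.
- *Lower power.* By the normal approximation, 87% power needs 24 per arm, and 24 / 0.90 = 26.7, so 27. The figure therefore includes the loss only if the design power is about 87%, not the stated 90%.
- *The earlier Australian trial.* The Sampling section cites it as a further basis but takes no figure from it that could account for the allowance.

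**The case against.** The strongest reply has three parts.

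*The text does not literally say that 54 includes the loss.* The two sentences are separate, and 54 might be the requirement before a larger recruitment target. The planned flowchart, where such a target could appear, is not available in the text reviewed. This is a fair point about wording, but it does not remove the conflict. If 54 is the figure before loss, the randomised number should be 58 to 60, and the abstract says 27 and 27. If 54 is the figure after loss, the stated 90% is not met.

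*The 86% is conditional.* It assumes that the full 10% is lost, that lost schools contribute no information, and that the comparison is unadjusted. For the continuous outcomes the Statistical Analysis section plans a baseline-adjusted analysis with multiple imputation. If d is in units of the follow-up standard deviation, a baseline to follow-up correlation of 0.3 would give 89.2% power with 24 per arm, and 0.5 would give 94.1%. That stands as a limit on the size of the problem. But the protocol states no correlation, does not say which standard deviation d refers to, and claims no such gain. If d were in units of the standard deviation of change, the condition would run the other way: adjustment would restore 90% only for a correlation of at most about 0.77. Choosing a correlation now, with the data collected, would be justification after the fact. Multiple imputation does not by itself restore the information in lost outcomes.

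*The shortfall is small and changes no analysis.* This is true. No estimate, test or error rate is affected, and reported confidence intervals will show the precision achieved. A printed design figure that contradicts its own inputs still needs correcting.

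**Conclusion.** The point holds. With the plan's own inputs and a two-sided test, 27 per arm is the number for 90% power with complete follow-up, and the 10% allowance is not in it. Under that loss, power for d = 0.90 falls by just under 4 points to about 86% (87.7% by the normal approximation), and the effect detectable with 90% power moves from 0.90 to 0.96.

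This rests on four assumptions: two-sided 5% testing, which is inferred; loss of the full 10%; no information from lost schools; and an unadjusted comparison of means. It describes a continuous outcome such as the hygiene score. It says nothing direct about power for menu composition, the other primary outcome, which is to be analysed by ordinal regression.

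**What to change.** Correct the Sampling section, and carry the same statement into the results paper. Suggested wording: *54 schools (27 per arm) give 90% power to detect d = 0.90 at a two-sided 5% level only with complete follow-up. With the anticipated 10% loss, about 24 schools per arm remain, giving about 86% power for d = 0.90, or 90% power for d = 0.96, in an unadjusted comparison.* Remove the suggestion that 54 already contains the allowance. If a larger recruitment target did exist, state it and reconcile it with the 27 and 27 in the abstract.

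The cost is one sentence in each place. Data collection is complete, so no schools are added and the planned analyses do not change; the stated power simply becomes slightly less favourable.

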### Randomization and Allocation

Randomization will use a minimization process [42] to balance the number of schools between the 2 groups. This approach ensures an excellent balance between groups for several prognostic factors, even in small samples. According to Egbewale [43], the minimization process makes the evaluated groups similar in important characteristics, mainly in trials that involve a small sample and have several prognostic factors to be balanced [38,44]. This procedure decreases the chances of significant discrepancies in baseline prognostic factors that may occur at random [45]. Minimization also controls the imbalances in baseline variables more efficiently than simple randomization, since, in small samples, simple randomization can produce a biased and misleading effect [43,46].

To maintain the balance between groups and prevent disproportionate distribution from occurring, 4 predictors of interest for the allocation will be considered: city, cafeteria administration (school-owned versus outsourced), school scope (public versus private), and the number of students (<500 students versus ≥500 students). An independent researcher will perform the randomization by minimization using a computer-generated technique in SPSS 26 (IBM Corp, Armonk, NY), avoiding possible influence on the allocation. The randomization unit will be schools with cafeterias.

As it will be an educational intervention, the researchers in charge of administering the interventions and assessing the outcomes will not be able to be blinded. Therefore, to avoid interference between the control and intervention groups, blindness will be arranged for the statistician in charge of data randomization and analysis. Participant flow during each stage of the study can be seen in the estimated study flowchart in Figure 1.

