#### Primary Outcomes

The assessment of the impact of the intervention on the composition of the menu offered in school cafeterias will be based on similar Australian studies [25,54]. The assessment of the school cafeteria menu composition will be determined by counting all items sold and the percentages of food classified according to the level of industrial processing proposed by the Food Guide for the Brazilian Population [51] and Monteiro et al [55]. A modified version of these references was used for this research. Group 1 (F*fresh*) includes fresh foods, minimally processed and culinary preparations without the addition of culinary ingredients (salt, sugar, oils, fats, or other ingredients). Group 2 (F*process*) includes processed foods and culinary preparations with culinary ingredients. Group 3 (F*ultra*) includes ultraprocessed foods. The culinary ingredients group proposed by Brazil [31] was excluded from the classification because the cafeterias do not sell these foods in isolation. Two properly trained dietitians will carry out this assessment using pen and paper. In case of divergence, a third dietitian will be consulted.

Good practices in food handling are a set of procedures that food services implement to ensure food quality to the consumer, minimizing possible harm to health, especially that caused by foodborne diseases. In this sense, there is a need to assess and classify the food sold according to the characteristics that include the amount of microbial and chemical contamination [56]. To collect data regarding hygienic conditions, we will use an instrument that has been validated by the National Health Surveillance Agency [57], which is based on Brazilian legislation, Regulatory Ordinance 817, published on May 10, 2013, by the Ministry of Health [56]. This legislation is composed of 51 items from 9 categories: water supply; building structure; cleaning of facilities, equipment, furniture, and utensils; control of vectors and urban pests; food handlers; raw material, ingredients, and packaging; food preparation; storage, transport, and display of prepared food; and liability, documentation, and registration.

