The assessment of the hygienic conditions of the cafeterias consists of a continuous scoring system that ranges from 0 (less severe) to 2498.89 (more severe). The score will be assigned when the evaluated cafeteria does not meet some of the requested requirements, so the higher the score, the greater the number of nonconformities verified and the worse the performance of the establishment [58]. The scores for each of the 51 items checked will be defined based on risk criteria, in order to identify those that have the most direct impact on the quality of food and on the health of consumers. In the score, the Impact Index will be used, representing the importance in the prevention of foodborne diseases, as well as the Factor Load of the items, as validated by the National Health Surveillance Agency [57]. This assessment will take place through an onsite inspection carried out by a trained dietitian using a printed checklist.

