#### Secondary Outcome

To assess the impact of the intervention on the food sold in the cafeteria, we have prepared a score that can be calculated based on the frequency of food available for sale and its classification according to the level of industrial processing proposed by Brazil [51] and Monteiro et al [55]. This score was developed due to the lack of a standard method for analyzing food in the school environment [59] and was also based on similar Australian studies [25,26]. Therefore, in addition to evaluating the composition of the menu offered in primary outcomes, we also chose to develop an equation that uses the frequency of each type of food but makes these variables continuous for a secondary outcome.

After data collection, all types of food and drinks sold in the cafeterias will be classified according to their level of processing. In the second stage, for each cafeteria, the frequency of items available in each category will be counted, multiplied by the standardized weight for the Group of fresh foods, Group of processed foods, and Group of ultraprocessed foods, which are +1, 0, and -1, respectively, as they are healthy, neutral, and unhealthy, respectively.

Equation (1) is used to calculate the score of the cafeteria for the level of food processing, where F*fresh* = frequency of fresh food items; F*process* = frequency of processed foods; F*ultra* = frequency of ultraprocessed foods; n = total number of items sold in the cafeteria, achieved by multiplying the frequency of food in each category by its corresponding weight, added to the values and dividing by the total number of items sold in the cafeteria. The score formula 50R + 50 is used to obtain scores for each establishment.

The score can vary on a scale of 0 to 100 points, where 50 is the midpoint. Thus, a cafeteria that offers healthy (fresh) and unhealthy (ultraprocessed) food in equal quantities will receive an average score of 50 points and will be considered a neutral cafeteria. Cafeterias that reach a score below 50 points have a greater predominance of ultraprocessed foods (ie, a greater offering of unhealthy foods). In summary, higher scores reflect better food quality in the school cafeterias.

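### The reason given for not blinding outcome assessors does not cover the paper-based sorting of foods by processing level, which could be masked

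*Protocol article*

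**What the plan says.** In the protocol article, Randomization and Allocation opens the blinding statement with "As it will be an educational intervention" and concludes that "the researchers in charge of administering the interventions and assessing the outcomes will not be able to be blinded". It gives no other reason. The one blinding measure is that "blindness will be arranged for the statistician in charge of data randomization and analysis".

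Primary Outcomes describes two different kinds of assessment:

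- **Menu composition (primary outcome 1):** all items sold are counted and assigned to one of three processing groups. "Two properly trained dietitians will carry out this assessment using pen and paper", and "In case of divergence, a third dietitian will be consulted".
- **Hygienic conditions (primary outcome 2):** "This assessment will take place through an onsite inspection carried out by a trained dietitian using a printed checklist".

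Secondary Outcome uses the same three groups and says when the sorting happens: "After data collection, all types of food and drinks sold in the cafeterias will be classified according to their level of processing". The groups are weighted +1, 0 and -1, and "The score formula 50R + 50 is used to obtain scores for each establishment".

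**The concern.** An educational programme reveals the allocation to those who teach it and those who take it. It does not reveal it to a person sorting a written list of foods, unless that person is told the school or arm. The article applies one reason to all outcome assessment, and so gives up masking in a step where the reason does not apply.

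The step is open to influence. The classification is a modified version of the published one. The line between the first two groups depends on whether a preparation contains added culinary ingredients, and the article itself expects raters to disagree. If raters know the arm, doubtful items could be resolved differently in the two groups, and the comparison would read the difference as an effect. The menu composition result and the only secondary outcome both depend on this step.

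**Working it through.** **Does the stated reason reach the classification step?** Setting the sections side by side:

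1. Randomization and Allocation: assessors cannot be blinded, because the intervention is educational.
2. Primary Outcomes: the menu is classified by two dietitians on paper, with a third for disagreements.
3. Secondary Outcome: classification into these groups follows data collection.
4. No section says that the classifiers must know school, arm or visit, and none provides for coded lists.

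The impossibility claimed in item 1 therefore does not follow from the procedure in items 2 and 3. It is easier to defend for the hygiene inspection, where the assessor is physically in the cafeteria.

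**Can later steps remove the bias?** The statistician receives foods already classified, so blinding at that stage comes too late. Adjustment for baseline, intention-to-treat analysis and multiple imputation (Statistical Analysis) do not correct a difference between arms in how follow-up items were classified.

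**How sensitive is the secondary score?** The inputs are the weights +1, 0 and -1 and the 50R + 50 formula, from Secondary Outcome.

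- R = (F_fresh − F_ultra)/n and score = 50 + 50R.
- Check against the article's own scale: all fresh gives R = 1 and a score of 100; all ultraprocessed gives R = −1 and 0; equal numbers of each give R = 0 and 50. This matches the stated range of 0 to 100 with midpoint 50.
- Moving one item by one group changes F_fresh − F_ultra by 1, so R changes by 1/n and the score by 50/n. For an assumed 10, 20, 30 or 40 items, that is 5.0, 2.5, 1.7 or 1.25 points per item.
- Moving a share q of items by one group, all in the same direction, changes the score by 50q. With q = 0.05, 50 × 0.05 = 2.5 points. With q = 0.10, 5.0 points.

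The item counts and values of q are assumptions; the article gives neither. It also gives no standard deviation for the score, so these points cannot be turned into a standardised effect from the document. No corresponding effect estimate is offered for menu composition, which is to be analysed by ordinal logistic regression.

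**The case against.** **Existing safeguards.** The classification follows published criteria in modified form, uses two trained raters and has third-rater adjudication. Baseline data are collected before randomization (Data Collection and Management), so arm cannot influence what is recorded at baseline. These points stand and make a large systematic shift less likely. They do not replace masking, since two raters and an adjudicator who all know the arm can lean the same way.

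**Who the classifiers are.** The blinding statement speaks of researchers and the classification section of dietitians. Reading the first to include the second is natural but not explicit. A reader might infer that the classifiers belong to the team delivering the programme, but nothing in the article says so. Nor does it say whether they also collect data on site.

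**Size relative to the planned effect.** It is tempting to assume a standard deviation of 10 to 15 points, turn 2.5 points into 0.17 to 0.25 SD, and call that 19% to 28% of the planned effect of 0.90. The document does not support this. Sampling bases the 0.90 on the primary outcomes, while the score is secondary, and the standard deviations have no source in the article.

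**Risk in the remedy.** A single dictionary keyed on item name would be wrong. The same named preparation can belong to different groups depending on added ingredients, so such a dictionary could hide a real change. This objection stands, and the fix below allows for it.

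**Conclusion.** The concern holds in a limited form. The article's reason for not blinding assessors does not justify unmasked sorting of foods, a judgement-based step behind primary outcome 1 and the secondary score. Knowledge of arm could bias that step, and no later safeguard in the plan would remove the bias.

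The only size that can be stated is the sensitivity of the secondary score: 50q points, or 2.5 points if an assumed 5% of items move by one group in one arm. A reader might infer that the results are biased towards benefit; the document shows only that this is possible, and the size and direction of any actual shift are unknown. Nor does the point show that every outcome could have been masked. The hygiene inspection and the recording of items sold take place on site and are a separate matter.

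This is an avoidable weakness worth correcting, and it does not invalidate the trial.

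**What to change.** 1. Limit the statement in Randomization and Allocation to course delivery and on-site data collection.
2. Have the two planned dietitians and the adjudicator classify coded item lists with school, arm and visit removed. Keep recorded ingredient or preparation details with each item, so that preparations with the same name can fall in different groups.
3. The Results section says that data are collected and under analysis. If classification is already done, repeat it masked on the recorded lists, and use or report the masked result.
4. State as limitations that on-site recording of items sold and the hygiene inspection remain unblinded.

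The cost is some clerical re-coding and a classification pass by the kind of raters already planned, with no new school visits. The article gives no staffing or cost figures, so calling this small is a judgement. If the classifiers also collected the data on site, they may recognise some lists and masking would be only partial. Using other dietitians would avoid that but would need extra staff.
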